### Safety evaluation and blinding assessment

Safety evaluation will be based on events including fainting, severe pain, hematoma, local infection, and other feelings of discomfort. Any adverse event will be recorded in detail.To assess whether the sham control is successful, two centers will be randomly chosen to report the EA data by means of a blinded questionnaire (Figure 4). All participants from the two centers will be asked to complete the questionnaire within 5 minutes after any treatment session in the 4th and 8th week. The percentage of participants reporting EA data will be compared between the two groups and success of the blinding will be analyzed.

**Figure 4 F4:**
[figure not shown]
Blinding questionnaire.

### Sample size and statistical analysis

According to our pilot trial, the reduction of MRS after an 8-week treatment was 6.5 ± 9.96 (mean ± standard deviation) and 2.00 ± 7.39 for the acupuncture and sham acupuncture groups, respectively. Considering it is a multicenter trial, we expanded the standard deviation to 1.5 times to enhance the reliability of the study. As a minimum 5-point reduction in MRS is considered effective [23], to detect a reduction of 5 points with a two-sided 5% significance level and a power of 95%, 180 participants will be needed for each group (1:1 ratio) allowing for a 20% dropout rate.

Data from the 12 hospitals will be pooled and the Clinical Evaluation Center of China Academy of Chinese Medical Sciences in Beijing will conduct a statistical analysis. According to the principle of intention-to-treat (ITT), all randomized participants will be analyzed. All statistical analyses will be two-sided tests and the level of significance will be established at 0.05. SAS 9.1.3 (SAS Institute, Cary, NC, USA) and SPSS Ver.13.0 (SPSS Inc., Chicago, IL, USA) software will be used. Continuous data will be represented by the mean, standard deviation, median, minimum value, and maximum value; categorical data will be represented by percentages. For comparison with the baseline, a *t*-test or nonparametric test will be used for continuous data, and nonparametric tests for categorical data. For comparison of two independent samples a *t*-test or nonparametric test will be used for continuous data, and a χ^2^ test or the Fisher exact test will be used for categorical data. The multiple imputation method will be used to handle the missing data. The statistical methods are as follows:

1. Case distribution and compliance analysis: case distribution of both groups in every center will be described. The total drop-out rate and the drop-out rate due to adverse events, of both groups, will be compared using the Fisher exact test.

2. Analysis of baseline characteristics.

3. Analysis of compliance: according to recordings in the case report form, compliance of the two groups will be compared.

4. Analysis of efficiency: efficiency analysis will be based on the ITT population (all randomized participants). Subjects without any treatment after randomization or without any valid data of evaluation although treated will still be included in the analysis.

5. Analysis of primary outcome: the primary outcome is the change in MRS compared with baseline at the 8th week (the primary time frame) and at the 4th, 20th, and 32nd week (the secondary time frame). Analysis of covariance (for normal distributed data) or nonparametric tests (for abnormal distributed data) will be used to investigate whether EA is more effective than sham EA. To detect the center effect, a covariance model will be used. Further analysis will be done if there is a center effect.

6. Analysis of secondary outcomes: for each group, the mean 24-h hot flash score, MENQOL, and hormones will be compared with their baseline. A *t*-test or nonparametric test will be used for comparison between groups.

7. Subgroup analysis: subgroup analyses will be conducted according to the stage of MT (early stage and late stage) to observe EA’s influence on MRS and MENQOL at the 4th, 8th, 20th, and 32nd week for participants. Analysis of covariance or nonparametric tests will be used.

8. Analysis of blinding: the number and percentage of subjects choosing true EA in the two selected centers will be established. A χ^2^ test or nonparametric test will be used for comparison among groups.

9. Analysis of safety: according to adverse events listed in the case report form, an analysis will be done using the χ^2^ test or the Fisher exact test.

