### Participants

In total, 360 participants will be recruited in this trial.

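### The 180 per group is the sample size before dropout: with the planned 20% dropout, power for a 5-point difference is about 90%, not the stated 95%

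*Protocol article*

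**What the plan says.** The protocol article, under *Sample size and statistical analysis*, gives every input to the calculation:

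- The pilot reductions in MRS after 8 weeks were "6.5 ± 9.96 (mean ± standard deviation) and 2.00 ± 7.39 for the acupuncture and sham acupuncture groups" respectively.
- To allow for the multicentre setting, "we expanded the standard deviation to 1.5 times".
- The aim is "to detect a reduction of 5 points", at a two-sided 5% level and 95% power.
- The result is that "180 participants will be needed for each group (1:1 ratio) allowing for a 20% dropout rate".

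The *Participants* section fixes the same total: "In total, 360 participants will be recruited in this trial". The statistical section also plans an intention-to-treat analysis of everyone randomized, with multiple imputation for missing data. The primary outcome is to be analysed by analysis of covariance, or by a nonparametric test if the data are not normal.

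**The concern.** A sample size that includes a 20% dropout allowance should exceed the evaluable number by a factor of 1/0.8. Here the quoted number equals the evaluable number, so the allowance appears to be stated but not applied.

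What is at stake is the power claim for the primary comparison. If the trial finds no difference, readers will weigh that result against a design said to miss a true 5-point difference 5% of the time. Under the protocol's own dropout assumption it would miss it about twice as often.

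**Working it through.** **Inputs** (all from *Sample size and statistical analysis*): pilot SDs of change 9.96 and 7.39; SD multiplier 1.5; difference 5; two-sided alpha 0.05 (z = 1.960); power 95% (z = 1.645); allocation 1:1; dropout 20%.

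**Step 1. Inflated SDs.**

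- 9.96 × 1.5 = 14.94
- 7.39 × 1.5 = 11.085
- Sum of variances: 223.20 + 122.88 = 346.08

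**Step 2. Reproduce the protocol's figure.** For two means with unequal SDs,

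n per group = (1.960 + 1.645)² × 346.08 / 5² = 12.995 × 346.08 / 25 = 179.9.

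This rounds up to 180, the number in the protocol, with no dropout allowance. The noncentral t gives 181.

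**Step 3. Add the allowance.** 179.9 / 0.8 = 224.9, so 225 per group and 450 in total. The cruder multiplication by 1.2 gives 216 per group. Neither is 180.

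**Step 4. Power at the planned size.** 180 × 0.8 = 144 evaluable per group. The standard error is √(346.08/144) = 1.550, and 5/1.550 = 3.225. Power is Φ(3.225 − 1.960) = Φ(1.265) = 0.897. The noncentral t gives 0.895.

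| Evaluable per group | Week-8 loss | Power for 5 points (normal approximation) |
|---|---|---|
| 180 | 0% | 95.0% |
| 171 | 5% | 94.0% |
| 162 | 10% | 92.8% |
| 144 | 20% | 89.7% |

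**Step 5. Could 180 include dropout by another route?** With a 5-point difference, two-sided 5% and 95% power, these variants were tried:

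| SD used | n before dropout | n after dividing by 0.8 |
|---|---|---|
| Simple mean of the inflated SDs | 177 | 222 |
| Larger inflated SD for both groups | 233 | 292 |
| Smaller inflated SD for both groups | 128 | 160 |
| SDs not inflated | 80 | 100 |
| Variance rather than SD multiplied by 1.5 | 120 | 150 |

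None gives 180 after the allowance. Two routes that change a stated input do come close. A one-sided 5% test needs 150, and 150 × 1.2 = 180. Power of 90% needs 146, and 146/0.8 = 182.5, so 183. The first contradicts the stated two-sided test and the second the stated power. In both cases 144 evaluable women per group still have about 90% two-sided power.

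**The case against.** The strongest reply is that 89.7% describes an unadjusted comparison of change scores, whereas the protocol plans analysis of covariance. If baseline MRS is the covariate and explains about 20% of the variance in change (a correlation of about 0.45, since 1 − 144/179.9 = 0.20), 95% power is restored at 144 per group. This is a real possibility. But the sample size calculation uses raw change-score SDs and claims no such gain, the protocol does not name baseline MRS as the covariate, and it allows a nonparametric test instead. An unstated gain cannot stand in for an allowance the text says was made.

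Second, the protocol does not say when the 20% dropout occurs. Follow-up runs to week 32 and the primary time point is week 8, so fewer than 20% may be missing then. This stands: 89.7% is the figure if the full 20% is lost by week 8, and smaller losses give the intermediate values tabulated above. None of them makes 180 a number that allows for 20% dropout at 95% power.

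Third, multiple imputation keeps all 360 women in the analysis. It does not in general recreate the information in an unobserved week-8 MRS, although a week-4 value may recover some of it.

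Fourth, multiplying the SDs by 1.5 is already conservative: at the uninflated pilot SDs, 144 per group would give 99.8% power. But the protocol attributes that step to the multicentre setting, and the 180 already uses it up.

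Finally, the article shows no formula, so the omission of the allowance is inferred from the exact match. The conclusion does not depend on how 180 was reached.

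**Conclusion.** The point holds. On the protocol's stated inputs, 180 per group is the requirement with complete data, and the claim that it also covers 20% dropout at 95% power is wrong. The shortfall is 45 women per group (225 − 180) if 95% power is to survive the dropout. Equivalently, it is about 5 percentage points of power at the planned size, with the type II error rising from 5% to about 10%.

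This rests on the inflated pilot SDs being right, on an unadjusted two-sample comparison, and on the full 20% being missing at week 8 with no information recovered by imputation. The error lies in the justification. The effect on the design is moderate, since power stays close to 90%.

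**What to change.** Keep 360 participants and replace the claim with a statement such as: 180 per group gives 95% power to detect a 5-point difference at the two-sided 5% level if no one drops out, and about 90% if 20% drop out (144 evaluable per group). Remove the statement that 180 allows for 20% dropout at 95% power. This costs wording only: the stated power becomes less favourable, and no more women are enrolled.

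If the sponsor wishes to keep 95% power after 20% dropout, the number is 225 per group, 90 more women in total.

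As an optional addition, the power at the pilot's own difference could be given. For 6.5 − 2.00 = 4.5 points and 144 per group, 4.5/1.550 = 2.903 and Φ(2.903 − 1.960) = 0.827, or about 82% by the noncentral t. The correction does not depend on it.

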## Methods/design

This will be a prospective RCT conducted over 2 years (from June 2013–May 2015) and at 12 hospitals in China (Guang’anmen Hospital; The First Hospital Affiliated to Anhui University of Chinese Medicine; Guangdong Provincial Hospital of Traditional Chinese Medicine (TCM); Hubei Province Hospital of TCM; The First Hospital of Hunan University of Chinese Medicine; Hengyang Hospital of Hunan University of Chinese Medicine; Affiliated Hospital of Shandong University of TCM; Integrated TCM and Western Medicine of Shanxi University of TCM; Shanxi Province Hospital of TCM; Yueyang Hospital of Shanghai University of TCM; TCM Hospital of Yantai; and 3rd Hospital of Zhejiang Chinese Medical University).Participants experiencing MT will be recruited from the 12 centers by use of advertisements in newspapers, television, websites, and posters. Participants will be sent to a gynecologist who will make the diagnosis. A 1-week baseline assessment will include MRS, Menopause-Specific Quality of Life Questionnaire score (MENQOL), average 24-h hot flash score, and hormone levels (FSH, LH, FSH/LH, and E2, examined at days 2 to 4 of the menstrual period or any day for participants in menopause). Eligible participants will be randomized after their informed consents are obtained. Central randomization will be performed by the Clinical Evaluation Center of the China Academy of Chinese Medical Sciences in Beijing. Stratified block randomization will be made according to the hospital and a block size of six will be used. A random number will be immediately received by the acupuncturist by phone or online after the informed consent is signed. All of the participants, statisticians, outcome assessors, and the gynecologists are blinded to the allocation, except for the acupuncturists. The flowchart of the trial is presented in Figure 1.

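### Randomization is stratified by hospital, but the primary analysis does not commit to hospital in the model and lets the observed distribution choose the test

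*Protocol article*

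**What the plan says.** The Methods/design section of the Protocol article fixes the allocation scheme: "Stratified block randomization will be made according to the hospital and a block size of six will be used". There are 12 hospitals, and under Sample size and statistical analysis "Data from the 12 hospitals will be pooled".

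Item 5 of that section covers the primary outcome, the change in MRS, with week 8 as the primary time frame. It contains two rules that depend on the data:

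- **Choice of test.** "Analysis of covariance (for normal distributed data) or nonparametric tests (for abnormal distributed data) will be used". No covariates are listed for the ANCOVA, and the nonparametric test is not named.
- **Role of hospital.** "To detect the center effect, a covariance model will be used. Further analysis will be done if there is a center effect". The article does not say what counts as a center effect, or what the consequence would be for the primary result.

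The sample size paragraph sizes the trial on a 5-point difference in MRS reduction (two-sided 5%, 95% power). It plans an intention-to-treat analysis of all randomized women, with multiple imputation for missing data.

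**The concern.** Hospital is known to be part of the design before any outcome is seen. Once allocation is balanced within hospital, the matching analysis has hospital in the model from the start; there is nothing to detect first. Making its role depend on a result leaves the primary analysis open on a point that the design has already settled.

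The normality rule raises a second question. A mean difference adjusted for baseline and a rank comparison are different quantities, and only the first corresponds to the 5 points used for sizing. If the distribution of the data picks the test, the quantity reported as primary is not known in advance. It could also differ between weeks 4, 8, 20 and 32, since item 5 covers all four.

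At stake are a clearly fixed primary analysis and a small amount of power.

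**Working it through.** **Inputs from the Protocol article.** The SDs of MRS change are 9.96 (EA) and 7.39 (sham), each multiplied by 1.5. The difference is 5 points, alpha is two-sided 5%, power is 95%, there are 180 per arm with 20% dropout, and there are 12 hospitals.

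**Input not in the article.** The share of variance lying between hospitals (ICC) is assumed. I use 0.05 and 0.10, with 0 and 0.20 to show the range.

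**Step 1: the plan's own figure.** The inflated SDs are 14.94 and 11.085. The pooled SD is √[(14.94² + 11.085²)/2] = 13.15. Then n = 2 × (1.96 + 1.645)² × 13.15² / 5² ≈ 180 per arm. This is the stated number, but it is reached before any dropout allowance. That is a separate matter and does not affect this point. With 20% loss, 180 × 0.8 = 144 per arm remain, and power is Φ(5 / (13.15 × √(2/144)) − 1.96) = Φ(3.225 − 1.96) = 89.7%.

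**Step 2: effect of leaving hospital out.** Stratified allocation removes between-hospital variation from the treatment contrast, so the true standard error is smaller than the naive one by the factor √(1 − ICC). A model without hospital still uses the larger one. It overstates the standard error by 1/√(1 − ICC), which is 1.026 at ICC 0.05 and 1.054 at ICC 0.10. With the total SD held at 13.15:

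- true alpha without hospital = 2 × [1 − Φ(1.96/√(1 − ICC))]
- power without hospital = Φ((3.225 − 1.96)/√(1 − ICC))
- power with hospital = Φ(3.225/√(1 − ICC) − 1.96)

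| Assumed ICC | True alpha, no hospital | Power at 144 per arm, no hospital | Power at 144 per arm, with hospital |
|---|---|---|---|
| 0 | 5.0% | 89.7% | 89.7% |
| 0.05 | 4.4% | 90.3% | 91.1% |
| 0.10 | 3.9% | 90.9% | 92.5% |
| 0.20 | 2.8% | 92.1% | 95.0% |

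Baseline MRS is left out of both models here, so that the table isolates hospital.

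**Step 3: simulation.** The setting was 12 hospitals of 30 women (360/12), blocks of six, normal data and 4,000 runs per setting. Alpha at ICC 0.05 and 0.10 was 4.8% and 3.9% for the unadjusted t-test, and 5.1% and 3.9% for the unstratified rank-sum test. The hospital-adjusted model stayed between 4.7% and 5.3% over all ICCs tried. With all 360 analysed and ICC 0.10, power was 96.2% unadjusted, 97.2% adjusted and 95.4% for the rank-sum test. At 5% the simulation error is about √(0.05 × 0.95/4000) = 0.3 percentage points, so the simulation agrees with the formulas.

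**Step 4: is the normality switch needed?** The treatment estimate from ANCOVA is in essence a difference of two averages over 144 to 180 women each. Its sampling distribution is close to normal even when individual changes are not, so its validity does not depend on the condition that item 5 attaches to it.

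**The case against.** The best defence is that the article is silent rather than wrong. Item 5 lists no covariates, so hospital may already be meant to sit in the ANCOVA, and the sentence on the center effect may describe that same model. A stratified rank test would also fit the words used. Covariate lists commonly belong in the full protocol or the analysis plan, which are not shown. The further analysis might be no more than an exploratory look at treatment-by-hospital interaction.

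Much of this stands, and it rules out several stronger readings that a reader might infer:

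- **That the rank test certainly drops baseline MRS and hospital.** The article does not say so. It names no adjusted or stratified version, so this is only a possibility.
- **That the center step produces a competing primary p-value.** Nothing says that the further analysis would replace the primary result; its consequence is simply undefined.
- **That false positives are inflated.** Omitting hospital works in the opposite direction.
- **That the hospital share is very large.** The sample size paragraph says "Considering it is a multicenter trial, we expanded the standard deviation to 1.5 times". If the whole inflation were between-hospital variance, the share would be 1 − 1/1.5² = 56%. The article presents the factor as a general margin and gives no split of the variance, so this figure has no support.
- **That the cost of losing baseline follows from comparing ANCOVA with a t-test on change scores.** The stated fallback is nonparametric, and the usual formula assumes equal SDs at both visits. The pilot SDs in the Background section are far apart (14.82 and 4.47 for EA; 13.03 and 7.85 for sham).

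How to combine a rank test over imputed data sets is also a detail for the analysis plan, and I do not count it.

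What the defence does not remove is the two conditional rules themselves. They are stated, not omitted. An analysis plan that put hospital in the model unconditionally and used ANCOVA whatever the distribution would replace item 5 rather than fill it in.

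**Conclusion.** The point holds in a limited form. Item 5 does not commit to the stratification factor in the primary test, leaves the consequence of a center effect undefined, and lets the observed distribution choose a test that may target a quantity other than the one the trial was sized on.

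The numerical harm from omitting hospital is small and in the safe direction: about 0.8 to 1.6 points of power at 144 per arm (91.1 − 90.3 and 92.5 − 90.9), with alpha slightly below nominal. These figures rest on an assumed ICC of 0.05–0.10, a total SD of 13.15, and equal recruitment across hospitals in the simulation. The main reason to change the text is that the primary analysis and its estimand should be settled before the data are seen. The change should be made because it costs almost nothing; the present wording does not invalidate the trial.

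**What to change.** State one primary analysis: ANCOVA of the week-8 change in MRS on treatment, baseline MRS and hospital (12 levels), in the intention-to-treat set with multiple imputation, whatever the normality or center-effect result. Remove the center-effect condition and report the treatment-by-hospital interaction descriptively. Keep a rank test stratified by hospital (van Elteren) as a sensitivity analysis only.

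The cost is wording and 12 − 1 = 11 degrees of freedom, out of about 288 (2 × 144) to 360 observations. No further participants are needed for this change. The Trial status section reports 80 women recruited, so the wording could be settled before unblinding.

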### Outcome

The primary outcome is the change in the MRS compared with baseline at the 8th week (the primary time frame) and at the 4th, 20th, and 32nd week (the secondary time frame). The secondary outcomes include changes in the average 24-h hot flash score [22] (1-week sum score divided by 7, evaluated at the 4th, 8th, 20th, and 32nd week), MENQOL (at the 4th, 8th, 20th, and 32nd week), and FSH, LH, FSH/LH, and E2 (examined at days 2 to 4 of the menstrual period or for participants in menopause, at the end of the 8th week) compared with baseline.

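### Secondary outcomes are compared between groups without a baseline or hospital term, which is valid but gives up precision, and the within-group tests beside them cannot show an effect of EA over sham

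*Protocol article*

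**What the plan says.** All places are in the Protocol article.

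- **Sample size and statistical analysis, item 6** gives two analyses for the secondary outcomes. The first is within arms: in each arm, "the mean 24-h hot flash score, MENQOL, and hormones will be compared with their baseline". The second is between arms, where a t-test or "nonparametric test will be used for comparison between groups".
- **The general paragraph of the same section** makes the comparison with baseline a formal test: a t-test "test or nonparametric test will be used for continuous data, and nonparametric tests for categorical data". All tests are two-sided at 0.05.
- **Outcome** defines these endpoints as changes from baseline: "The secondary outcomes include changes in the average 24-h hot flash score", followed by MENQOL and the hormones.
- **Methods/design** confirms that every baseline exists: "A 1-week baseline assessment will include MRS, Menopause-Specific Quality of Life Questionnaire score (MENQOL), average 24-h hot flash score, and hormone levels". The same section stratifies randomisation by hospital, in blocks of six.
- **Item 5**, for MRS, plans ANCOVA if the data are normal; otherwise "nonparametric tests (for abnormal distributed data) will be used to investigate whether EA is more effective than sham EA". It adds: "To detect the center effect, a covariance model will be used".
- **Item 7** plans ANCOVA or nonparametric tests for MRS and MENQOL within the early and late MT subgroups.

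**The concern.** MENQOL gets a t-test or nonparametric test in the whole trial but may get ANCOVA in the subgroups, so the less efficient method serves the main comparison. Hot flash score and hormones are never given a covariate model, and the centre model stands only under the primary outcome. The article gives no reason for these differences.

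Three things are at stake:

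1. Precision on outcomes that the trial sets out to inform. The hormones belong to the second objective in the Background, and quality of life is an aim in the Discussion.
2. Sensitivity of each secondary comparison to chance imbalance at baseline.
3. A set of p-values for change within each arm. Both arms can be significant when EA equals sham, because sham response, natural course and regression to the mean all contribute to change from baseline.

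**Working it through.** **Figures in the plan.** The article states no power, SD or correlation for any secondary outcome, so there is no planned figure to reproduce. The 180 per arm is the stated size for MRS and is used here only as the number randomised.

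**Assumptions.** Baseline/follow-up correlation r = 0.3, 0.5 or 0.7; equal SDs at both times, scaled to 1; between-hospital share of variance (ICC) 0.01 to 0.15.

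**1. Precision against change scores.** Variance of a change is 2(1 − r). Residual variance after ANCOVA on baseline is 1 − r². The ratio is (1 − r²) / [2(1 − r)] = (1 + r)/2.

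| r | ratio | ANCOVA n per arm matching 180 |
|---|---|---|
| 0.3 | 0.65 | 117 |
| 0.5 | 0.75 | 135 |
| 0.7 | 0.85 | 153 |

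At r = 0.5, take an effect that the change-score test detects with 80% power. The standardised effect is 1.960 + 0.842 = 2.802. Under ANCOVA it becomes 2.802/√0.75 = 3.235, so power is Φ(3.235 − 1.960) = Φ(1.275), about 90%.

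If the t-test were run on follow-up values instead, the ratio would be 1 − r² = 0.91, 0.75 or 0.51.

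**2. Chance imbalance.** The standard error of a baseline difference is √(2/180) = 0.105 SD. A gap of 0.2 SD is therefore 0.2/0.105 = 1.9 standard errors, which is fairly extreme. Given such a gap, a change-score comparison shifts by (1 − r) × 0.2 = 0.14, 0.10 or 0.06 SD for r = 0.3, 0.5 or 0.7.

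A typical gap is smaller. The expected absolute gap is 0.105 × √(2/π) = 0.084 SD, which at r = 0.5 gives a shift of 0.042 SD. At r = 0.5 the change has SD √(2 × 0.5) = 1, so the comparison has standard error 0.105 SD. The typical shift is 0.042/0.105 = 0.40 of that.

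**3. Hospital omitted after stratifying on it.** The true type I error of a nominal 5% test is 2[1 − Φ(1.96/√(1 − ICC))]. This is 4.9% at ICC 0.01, 4.4% at 0.05, 3.9% at 0.10 and 3.4% at 0.15. The departure is on the conservative side.

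**4. Within-group tests.** The article gives no pilot data on the secondary outcomes, so the pilot sham change in MRS (2.00, SD 7.39, n = 8) serves only as an illustration. The chance that a sham arm with that true change is significant against its own baseline is Φ(2.00 × √n / SD − 1.96):

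- n = 180, SD 7.39: Φ(3.63 − 1.96) = 0.95.
- n = 180, SD inflated by the plan's factor of 1.5 to 11.085: Φ(2.42 − 1.96) = 0.68.

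A sham arm can thus readily be significant against baseline, so the same result in the EA arm is not evidence for EA over sham.

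**The case against.** The strongest defence is that the planned between-group comparison is an accepted and valid analysis. The endpoints are defined as changes, so the t-test can be read as a test on change scores, which already use the baseline by subtraction. Over randomisation the test is unbiased and does not inflate type I error. This stands. A reader might infer that the secondary results will be biased or prone to false positives, but the documents do not support that. The shift in step 2 of the working is conditional on an observed imbalance, 0.2 SD is close to a worst case, and leaving out hospital errs towards caution.

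Second, the size of the precision loss rests on assumed correlations and equal SDs, and hormones may well be skewed. This also stands: the figures are a range and not an estimate for this trial.

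Third, a reader might infer that efficacy will be judged on within-arm p-values. The plan does not say so. Item 6 pairs those tests with a between-group comparison in its next sentence, and the Background frames the trial as EA against sham EA. What remains is that the planned within-arm tests answer no question of the trial and leave room for misreading.

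Fourth, the trial is sized on MRS, whose analysis already provides for ANCOVA and a centre model, so the primary conclusion is untouched. That limits the importance of the point but is no reason to analyse the secondary outcomes less efficiently.

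The choice is not merely a detail left to an unseen analysis plan, because item 6 itself names the tests.

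**Conclusion.** The point holds as a matter of efficiency and clarity, not validity. Item 6 fixes a between-group analysis for all secondary outcomes that uses neither the baseline as a covariate nor the stratification factor, while neighbouring items plan ANCOVA for MRS and for MENQOL in the subgroups.

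Under equal SDs and a correlation of 0.3 to 0.7, change scores give up 15% to 35% of variance that ANCOVA would remove. Conditional on a fairly extreme 0.2 SD baseline gap, the estimate moves by 0.14 to 0.06 SD; typical gaps do less. The missing hospital term costs a little power through a slightly conservative test. The within-group tests carry no information on EA against sham.

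Confidence is high on what item 6 says. It is lower on the size of the loss, because the article gives no correlations or hospital variances for these outcomes.

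**What to change.** Reword item 6 so that:

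- each secondary outcome is analysed by ANCOVA on treatment, its own baseline value and hospital;
- skewed outcomes, the hormones in particular, are log-transformed or analysed by a rank-based ANCOVA;
- the result reported is the between-group difference with its 95% CI;
- changes within each arm are given as descriptive statistics without p-values.

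This also aligns the whole-trial analysis of MENQOL with the ANCOVA planned for it in item 7.

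The cost is analysis wording only: no new data, visits or participants. The article reports 80 of 360 participants recruited and statisticians blinded to allocation, so at that stage the change could still be specified in advance.
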